# Securing jugular central venous access devices with dressings fixed to a liquid adhesive in an intensive care unit population: a randomised controlled trial

**DOI:** 10.1186/s13063-022-06322-9

**Published:** 2022-05-12

**Keywords:** Central venous access device, Dressing failure, Intensive care unit

## Abstract

**Background:**

Central venous access devices (CVADs) can have high rates of failure due to dressing-related complications. CVADs placed in the internal jugular vein are at particular risk of dressing failure-related complications, including catheter-associated bloodstream infection and medical adhesive-related skin injury. Application of Mastisol liquid adhesive (MLA) may reduce CVAD dressing failure and associated complications, by reducing the frequency of dressing changes. The aim of this study is to investigate whether, in an intensive care unit (ICU) population, standard dressing care with or without the addition of MLA, improves internal jugular CVAD dressing adherence.

**Methods:**

This two-arm, parallel group randomised controlled trial will be conducted in three Australian ICUs. A total of 160 patients (80 per group) will be enrolled in accordance with study inclusion and exclusion criteria. Patients will be randomised to receive either (1) ‘standard’ (in accordance with local hospital policy) CVAD dressings (control) or (2) ‘standard’ dressings in addition to MLA (intervention). Patients will be followed from the time of CVAD insertion to 48 h after CVAD removal. The primary outcome is ‘dressing failure’ defined as requirement for initial CVAD dressing to be replaced prior to seven days (routine replacement).

**Discussion:**

This study will be the first randomised controlled trial to evaluate the clinical effectiveness of MLA in the adult intensive care unit population and will also provide crucial data for patient-important outcomes such as infection and skin injury.

**Trial registration:**

Australian New Zealand Clinical Trials Registry ACTRN12621001012864. Registered on 2 August 2021

## Introduction

### Background and rationale

Central venous access devices (CVADs) are used extensively worldwide to deliver critical treatment and haemodynamic monitoring [1, 2]. They are a frequently consumed medical device in hospitals, with more than 130,000 used in Australian public hospitals each year [3]. CVADs are inserted into large veins of the neck, chest, arm or groin and terminate in the central vasculature [1, 4]. Despite their utility, these important medical devices frequently result in complications, with reported device failure of up to 30% due to complications such as dislodgement, blockage/occlusion, fracture/breakage, thrombosis, pleural/pericardial effusion or infection [1, 2, 5]. These complications typically result in delayed treatment due to the need for reinsertion, causing extended admission time, increased healthcare costs, venous depletion and increased morbidity and mortality [6].

Although the placement of CVADs in the jugular vein has been associated with an increased risk of central line associated bloodstream infection (CLABSI) and device failure compared to placement in the subclavian vein [2, 7, 8], the jugular vein remains a frequently selected site for CVAD placement in intensive care units (ICUs). This device failure may be attributed, in part, to inadequate dressing of the CVAD, resulting in (1) catheter dislodgement and (2) micromotion leading to complications such as occlusion, venous thrombosis, catheter rupture and infection [9]**.**

Traditional practice for dressing and securement of internal jugular (IJ) CVADs has been the use of polyurethane transparent dressings with or without additional securement from sutures or commercial sutureless stabilisation devices [9]. However, current dressing and securement practices are often inadequate, as IJ CVAD dressings frequently fail as a result of diaphoresis, beard growth, multi-vector pull forces related to the ‘drag’ of multiple infusion lines, intermittent ‘catching’ on objects and increasingly early mobilisation of ICU patients [2, 10, 11]. Each time a dressing fails it requires replacement, therefore placing patients at a higher risk of medical adhesive-related skin injury (MARSI) [12]. CVAD-related MARSI typically includes bruising, local site infections, pressure injuries, maceration, dermatitis, and mechanical injuries such as skin tears and blisters which have the potential to be disfiguring and lead to CVAD failure [13, 14]. Furthermore, dressing failure creates an opportunity for skin bacteria to contaminate the catheter insertion site leading to CLABSI or local infection, with a threefold increased risk of CLABSI as a result of skin colonisation and the migration of organisms down the catheter following disruption of the second dressing [15].

Mastisol liquid adhesive (MLA) (Eloquest Healthcare, Inc., Ferndale, MI) is a non-water-soluble gum mastic liquid adhesive designed to improve dressing adherence and integrity [12] and consequently decrease dressing failure. MLA is applied to the skin under the dressing after skin antisepsis. The purpose of MLA is to reduce frequent and often painful dressing changes and the resulting incidence of both CLABSI and MARSI [12], by improving dressing adhesion. A recent study in healthy volunteers found no statistical difference in bacterial growth with the use of MLA compared to standard care alone, supporting its safe use in this patient population [12]. Furthermore, a recent audit of IJ CVADs dressings in a cardiovascular ICU found an improvement with dressing adhesion from 11% (*n* = 4) to 100% (*n* = 30) with the use of MLA [16]. However, despite being in clinical use in Australia for many years, MLA has not been tested rigorously in a randomised controlled trial (RCT). To determine if MLA is a clinical and cost-effective intervention to improve IJ CVAD dressing adherence, we propose a multi-centre, two-arm, parallel group RCT.

### Objectives

The objectives of this study are to:Assess the effectiveness of MLA, compared to ‘standard’ dressing care, in reducing number of dressing changes, adverse events, clinician workload and costs in associated with IJ CVADsEvaluate the acceptability of MLA to adult ICU patients and clinicians

### Trial design

The trial design is as follows: multi-centre, superiority, two-arm, parallel group RCT.

## Methods: participants, interventions and outcomes

### Study setting

This study will be undertaken at the following tertiary-level academic teaching hospitals in Australia:The Prince Charles Hospital, Chermside, QueenslandLogan Hospital, Meadowbrook, QueenslandLiverpool Hospital, Liverpool, New South Wales

### Eligibility criteria

Patients will be eligible for inclusion in the study if they are≥ 18 years oldExpected to require an IJ CVAD for ≥ 72 hRequire ≥ 24 h treatment in the ICUScreened within 12 h of CVAD insertion

Patients will be excluded if theyHave a CVAD inserted under emergency conditionsHave a current bloodstream infection diagnosed within 24 h prior to CVAD insertion,Have a pre-existing concurrent CVAD expected to dwell for > 24 hAre receiving end-of-life careHave previously been enrolled in the study

### Who will take informed consent?

Research staff will screen patients according to inclusion and exclusion criteria. If eligible, patients will be approached by research staff for informed consent. If the patient does not have capacity to provide consent, the patient’s substitute decision maker will be approached. If prospective consent is not able to be obtained from either the patient or their substitute decision maker within the inclusion criteria time frame, the patients will be enrolled in the trial under a ‘consent to continue’ model as approved by the reviewing Human Research Ethics Committee (HREC). The patient and/or their substitute decision maker will then be approached for consent either in person (preferred) or by phone as soon as possible after enrolment.

### Additional consent provisions for the collection and use of participant data and biological specimens

Not applicable.

### Interventions

#### Comparators

Control: ‘Standard’ CVAD dressings as per individual hospital policyIntervention: ‘Standard’ CVAD dressings in addition to MLA

### Intervention description

#### Control group

The control group will have their CVAD dressed and secured in accordance with standard hospital policy [17–19] and the individual needs of the participant.

#### Intervention group

The intervention group will have their CVAD dressed and secured in accordance with standard hospital policy, plus the use of MLA immediately prior to dressing application (all other products, including skin barrier products and sutures are permitted with MLA). MLA will be applied using the applicator as per manufacturer’s instructions (i.e. a single-layer border under the expected perimeter of the CVAD dressing).

### Criteria for discontinuing or modifying allocated interventions

Criteria for discontinuation or modification of interventions will be:Development of MARSI attributed to MLA, as ascertained by each site’s principal investigators and reviewed by the HRECDevelopment of CLABSI attributed to MLA, as ascertained by each site’s principal investigators and reviewed by the HREC

If a patient develops an adverse reaction thought to be the result of MLA, use of MLA will cease and the HREC, project manager and coordinating principal investigator notified.

### Strategies to improve adherence to interventions

Standardised education will be provided to both research and clinical staff at each site prior to study commencement to improve adherence to study interventions. Research staff will, where possible, be present for the first application of MLA on each patient and provide ongoing study information and resources to clinical staff responsible for CVAD dressing care throughout the duration of each CVAD dwell. Research staff will be available to be contacted outside of business hours to answer any questions or queries clinical staff may have. If MLA is not applied at the time of dressing change, a protocol deviation will be recorded, and MLA will be reapplied at the next dressing change.

### Permitted and prohibited concomitant cares

All concomitant cares will be permitted whilst the patient is enrolled in the trial. No cares will be prohibited.

### Post-trial care

After the CVAD is removed as clinically indicated, outcome and adverse event data will be collected for a further 48 h by research staff. After this time, no further post-trial care is required.

### Outcomes

#### Primary outcome

Dressing failure: defined as requirement for initial IJ CVAD dressing to be replaced due to the dressing lifting at the edges at any point during CVAD dwell but prior to scheduled dressing change (scheduled dressing changes are every seven days). The requirement for dressing changes will be determined by clinical staff treating the patient, and the clinical indication for dressing change will be recorded. If a patient’s CVAD is removed prior to seven days with the primary dressing still in situ, the dressing will be considered not to have failed.

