### Participant timeline

Participants are enrolled prior to or within 12 h of their CVAD insertion, and will continue on the study until 48 h after their CVAD is removed. It is anticipated that each CVAD will dwell for an average of 7 days, resulting in an average enrolment time for each participant of 9 days (including CVAD dwell whilst in ICU and on the ward).

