#### Implementation

A statistician independent of the research team will generate the randomisation allocation sequence, and this will be uploaded onto the randomisation service without viewing by the research team. Patients will be enrolled and randomised by members of the research team, with intervention allocation assigned as per the randomisation service.

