Age Weight Height APACHE II Score Skin type • Very fair, fair, medium, olive, etc. Skin integrity • Good, fair, poor Date of hospital and ICU admission ICU admission type • Planned, emergent, IHT Primary reason for ICU admission • Medical, surgical, other Number of comorbidities Current infections • Blood, urinary, respiratory, etc. Current wounds • Yes, no	CVAD insertion site • Left or right IJ Placement of CVAD in IJ vein • High, mid, low Angle of CVAD lumens • Down, up, horizontal Number of CVAD lumens Place of CVAD insertion • ICU, OT, etc. Antimicrobial-impregnated CVAD • Yes, no Inserter type • ICU registrar, ICU consultant, anaesthetic registrar, etc. Number of insertion attempts Technologies used during insertion • Ultrasound, x-ray, ECG, etc. Hair clipped prior to CVAD insertion • Yes, no Dressing site • Neck, chest, other Diaphoretic at insertion site • Yes, no Facial hair at insertion site • Yes, no Dressing and securements in addition to ‘standard care’ • Sutures, bordered transparent dressing, tissue adhesive, etc. Date and time of first MLA application Staff/patient satisfaction with dressing application • 0 = not at all satisfied, 10 = completely satisfied	Date/time of check Reason why check not able to be completed • Patient not available, etc. Is randomised dressing still in situ • Yes, no Dressing site • Neck, chest, other Dressing and securements in situ • Sutures, bordered transparent dressing, tissue adhesive, etc. Condition of current dressing • Clean, dry, intact, lifting at edges, etc. How many edges of the dressing are lifting or requiring reinforcement Complications at CVAD insertion site • Redness, purulent discharge, pain, etc. Has the patient mobilised, been diaphoretic, restless/agitated • Yes, no Signs and symptoms of skin injury/reaction • Pain, itch, redness, rash, papules, stripping, blister, etc. Suspected cause of MARSI or skin injury/reaction Extent of redness, rash or maceration if applicable Positive bloodstream infections since last daily check • Yes, no Number of administration sets What is the CVAD currently being used for • Fluids, blood products, CVP monitoring, blood sampling, etc. Dressing changes since last daily check • Date/time, reason for dressing change, staff/patient satisfaction, etc.	Date/time of CVC removal Reason for CVC removal • Treatment complete with/without complications, patient deceased, routine replacement, etc. Complications at time of CVC removal • Occlusion, unable to aspirate, accidental removal, suspected infection, MARSI, etc. Signs and symptoms of skin injury/reaction • Pain, itch, redness, etc. Extent of redness, rash or maceration if applicable Pain, tenderness, redness, swelling at CVC insertion site Patient mobility at time of CVC removal • Independent, requires assistance, bed-bound, etc. IV antibiotics administered during CVC dwell • Yes, no Patient diagnosed with delirium • Yes, no Staff/patient satisfaction with dressing removal • 0 = not at all satisfied, 10 = completely satisfied	Was the patient alive at 48 h after CVC removal? • Yes, no Date/time of death SAEs Results of CVC tip culture Results of CVC insertion site swabs Results of blood cultures

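### The primary outcome is tied to the initial dressing, but enrolment up to 12 h after insertion means that dressing can pre-date randomisation and carry no MLA

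*Protocol article*

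**What the plan says.** - **Outcome (Protocol article, Primary outcome).** Failure is "defined as requirement for initial IJ CVAD dressing to be replaced due to the dressing lifting at the edges", before the scheduled seven-day change. A device removed before seven days with its primary dressing still on counts as no failure.
- **Outcome (Abstract, Methods).** The wording is "requirement for initial CVAD dressing to be replaced prior to seven days (routine replacement"), without the condition that the edges lift. The same paragraph states: "Patients will be followed from the time of CVAD insertion".
- **Enrolment window (Participant timeline).** "Participants are enrolled prior to or within 12 h of their CVAD insertion". Eligibility criteria likewise require screening within 12 h of insertion.
- **Randomisation (Implementation).** "Patients will be enrolled and randomised by members of the research team". Allocation is concealed until then.
- **Intervention (Intervention group).** Standard care "plus the use of MLA immediately prior to dressing application".
- **Missed MLA (Strategies to improve adherence).** If MLA is omitted at a dressing change, a deviation is recorded and MLA is used at the next change. This does not cover a dressing already on at randomisation.
- **Data form (Table 1).** The daily check asks "Is randomised dressing still in situ". The insertion column records when MLA was first applied.

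**The concern.** A dressing placed before randomisation cannot contain allocated MLA. For a patient enrolled after insertion, that dressing is the initial one in the ordinary sense of the word. In the MLA arm two courses are then open, and the article does not say which applies.

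1. The dressing stays on. The primary outcome is observed on a dressing without MLA, and the treatment effect is diluted.
2. The dressing is exchanged to apply MLA. Under the Primary outcome section it was not replaced for lifting, so it has not failed. Under the abstract it was replaced before seven days, so it has.

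Controls face no such exchange. The intention-to-treat analysis keeps these patients, so whichever rule a site adopts enters the primary logistic regression. The Kaplan-Meier comparison of dressing failure needs a start time, and follow-up from insertion, an initial dressing and a randomised dressing point to different ones.

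**Working it through.** **Inputs.** From Sample size: control failure 50%, MLA failure 25%, alpha 0.05, power 90%, 77 per group plus 3, giving 80. The article does not give the share f of patients randomised after their first dressing. I assume f = 10%, 25% and 50%, and that a dressing without MLA fails at the control rate of 50%.

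**Step 1: reproduce the plan's figure.** Two-sided test, pooled variance, no continuity correction, mean proportion 0.375:

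n = [1.96·√(2·0.375·0.625) + 1.2816·√(0.5·0.5 + 0.25·0.75)]² / 0.25² = (1.3419 + 0.8477)² / 0.0625 = 76.7, so 77 per group. The stated size is correct for its inputs. Power is 90.1% at 77 and 91.2% at 80 per group.

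**Step 2: old dressing left on and scored.** MLA-arm failure = 0.25(1 − f) + 0.50f = 0.25 + 0.25f, so the difference shrinks to 25(1 − f) points. Power = Φ{[Δ√n − 1.96√(2p̄(1 − p̄))] / √(p₁(1 − p₁) + p₂(1 − p₂))} with n = 80:

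| f (assumed) | MLA-arm failure | Difference (points) | Power, 80 per arm |
|---|---|---|---|
| 0 | 25% | 25 | 91% |
| 10% | 27.5% | 22.5 | 84% |
| 25% | 31.25% | 18.75 | 68% |
| 50% | 37.5% | 12.5 | 36% |

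**Step 3: old dressing exchanged, every exchange scored literally (worst case).**

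- *Primary outcome section, no true effect (50% in both arms).* The exchanged dressing is never a failure, so MLA-arm failure = 0.50(1 − f) = 45%, 37.5% and 25%. The chance of a significant result favouring MLA is about 9%, 36% and 91%.
- *Abstract wording, true MLA failure 25%.* Every exchange is a failure, so MLA-arm failure = 0.25(1 − f) + f = 32.5%, 43.75% and 62.5%. The true benefit shrinks and, at f = 50%, reverses.

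The two wordings therefore push the estimate in opposite directions.

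**Step 4: earlier wear in controls.** Suppose the outcome follows the randomised dressing, and late controls keep a dressing up to 12 h old. If 50% fail over 168 h at a constant hazard (assumption), the risk in 12 h is 1 − 0.5^(12/168) = 4.8%. Across the control arm that is at most 0.048 × 0.50 = 2.4 points at f = 50% and about 0.5 points at f = 10%.

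**The case against.** The strongest reply is that the article shows what was meant. Table 1 tracks the randomised dressing and records first MLA application among the insertion data. Research staff are to attend the first MLA application where possible. The analysis section excludes randomised patients whose insertion is cancelled or fails, so randomisation before insertion is an expected route, and those patients are unaffected. Instructions for a dressing already in place could also sit in the full protocol, which is not shown. This makes the intended reading likely. It does not change the stated definition, which names a different object from the form, and the abstract repeats that object.

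Three stronger readings are tempting, and the documents do not support them.

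- *A reader might infer that failure will be scored on the wrong dressing.* The article does not say so. It follows from the wording only for patients randomised after their first dressing, and only if sites apply it literally.
- *A reader might infer that the endpoint differs by arm for every late patient.* If the old dressing stays on, both arms are scored on a dressing without MLA. That dilutes the effect but cannot by itself create a false benefit.
- *A reader might take the 91% or 62.5% in Step 3 as expected.* Both need f = 50%, every late MLA patient exchanged, every exchange scored literally, and the new MLA dressing never assessed. The clinical indication for each change is recorded, so an exchange made only to apply MLA should be identifiable.

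**Conclusion.** The point holds as a defect in a stated endpoint definition. The index dressing named in the outcome conflicts with the enrolment window, with the moment MLA is applied and with the term used in Table 1. For MLA patients randomised after their first dressing, the outcome is either measured on a dressing without MLA or undefined.

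The size depends on f, which is unknown. Under dilution, power at 80 per arm falls from about 91% to 84%, 68% and 36% at assumed f of 10%, 25% and 50%, taking the plan's 50% and 25% and a control-rate failure for dressings without MLA. Bias from literal scoring of exchanges can run either way and is a worst case. The sample size of 77 per group is not in error, and it stands if the index dressing is the randomised one.

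**What to change.** 1. In the Primary outcome section and the abstract, define the index dressing as the randomised dressing, matching Table 1, with one definition for both arms.
2. Set one time zero for both arms: the later of randomisation and application of the index dressing. Follow up to that dressing's scheduled change, and use the same origin for the Kaplan-Meier analysis. Randomisation alone will not serve as the origin, because patients randomised before insertion have no dressing yet.
3. Do not count as failure any lifting or replacement before time zero, or a replacement made only to apply the allocated regimen.
4. Record whether randomisation came before or after the first dressing, and add a sensitivity analysis restricted to patients randomised before it.

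How a dressing already in place at randomisation is managed must be reconciled by the investigators across Intervention group, Strategies to improve adherence, Primary outcome and Participant timeline. The index definition depends on that answer, and I propose no clinical rule.

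**Cost.** A paragraph of definition, one derived variable and one extra analysis. Observed wear is slightly shorter in controls randomised late, who may still carry up to 12 h of earlier wear (Step 4). Table 1 lists the time of first MLA application but not of randomisation. The web-based service probably stamps it, but this must be confirmed.

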#### Secondary outcomes

All-cause CVAD failure: a composite of failure resulting in CVAD removal. Includes pain, infiltration/extravasation, blockage/occlusion (with or without leakage), fracture, thrombosis, dislodgement (complete or partial), or haematomaIndividual types of CVAD failure resulting in CVAD removal [pain, infiltration/extravasation, blockage/occlusion (with or without leakage), fracture, thrombosis, or dislodgement (complete or partial)]‘Central line associated bloodstream infection’ defined as per the National Healthcare and Safety Network (NHSN) [20]‘Primary bloodstream infection’ defined as per the NHSN [20]‘Local infection’ as defined by the Centres for Disease Control and Prevention (CDC)/NHSN ‘Arterial or venous infection’ criteria [21]Loss of dressing integrity not requiring dressing change (i.e. lifting at edges with/without reinforcement required) assessed for all dressings per patientDressing dwell time (from dressing application to removal in days) assessed for all dressings per patientPremature dressing removal (before seven days from dressing application; all dressings per patient)Number of dressing changes (from first application to last removal; all dressings per patient)Device dwell-time (time from CVAD insertion to removal in hours)Serious adverse events (i.e. mortality, CLABSI, MARSI)Adverse skin events relating to MARSI (e.g. pain, itch, erythema, skin stripping, blister, skin tear, irritant contact dermatitis, maceration, folliculitis or infection) [22]Cost (cost and number of products used, cost of treating complications, staff time for device insertion), as informed by standard diagnosis related groups (DRGs), staff time estimates to apply and remove dressings and product costs.Staff and patient satisfaction on dressing application and removal (0 = not at all satisfied to 10 = completely satisfied) assessed at initial application, all dressing changes and final removal for all dressing changes per patient.Skin colonization, measured both descriptively (i.e. organism) and quantitatively (i.e. colony forming units)

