#### Adverse event reporting and harms

Enrolled patients will be monitored and treated for untoward medical occurrences in line with standard clinical care. Therefore, only adverse events which the treating clinicians believe are associated with the intervention will be reported.

In this trial, the following will be considered as serious adverse events (SAEs):DeathCLABSIMARSI

All SAEs from randomisation to 48 h after removal of the CVAD will be recorded on REDCap and reported to the coordinating centre within 24 h.

The minimum information to report will include:Patient study numberNature of the eventCommencement and cessation of eventThe principal investigator’s assessment of the relationship between the study intervention and the event (not related, possibly related, probably related)Whether treatment was required for the event and what treatment was administered

It is the responsibility of each site’s principal investigator to inform the chief investigator and project manager of all SAEs which occur at their site. Copies of reports and correspondence to and from the reviewing HREC and research governance will also be sent to the coordinating centre. The project manager will be responsible for reporting all SAEs to the reviewing HREC and alerting other participating sites of the SAE if required.

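### The all-cause CVAD failure composite omits removal for infection or MARSI, and the adverse event reporting rule cannot support a between-arm comparison of other non-serious events

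*Protocol article*

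**What the plan says.** **Composite.** Under Secondary outcomes, the protocol article defines "All-cause CVAD failure: a composite of failure resulting in CVAD removal". It then names pain, infiltration or extravasation, occlusion, fracture, thrombosis, dislodgement and haematoma. The next outcome, individual types of failure, repeats the list without haematoma. Neither list contains infection or MARSI. CLABSI, primary bloodstream infection and local infection are separate secondary outcomes defined by NHSN/CDC criteria.

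The Background and rationale describes device failure more widely. It attributes failure to "complications such as dislodgement, blockage/occlusion, fracture/breakage, thrombosis, pleural/pericardial effusion or infection", and says that MARSI-type injuries "have the potential to be disfiguring and lead to CVAD failure". In Table 1, the complications recorded at removal are "Occlusion, unable to aspirate, accidental removal, suspected infection, MARSI, etc".

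**Adverse events.** The first objective is to assess MLA "in reducing number of dressing changes, adverse events, clinician workload and costs". Under Plans for assessment and collection of outcomes, research staff collect adverse events at daily assessments, with no condition on attribution. Under Adverse event reporting and harms, "only adverse events which the treating clinicians believe are associated with the intervention will be reported". The same section lists death, CLABSI and MARSI as serious adverse events and records all of them, with a relatedness grade that includes a not-related category. The blinding section says that patients, clinicians and research staff cannot be blinded.

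**The concern.** An outcome called all-cause should count every removal for device failure. This one leaves out two complications that the Background says MLA is meant to reduce. The discontinuation criteria also allow that MLA might cause them, so an effect in either direction is contemplated. If infective or skin-related removals differ by arm, the composite as listed would not show it.

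For adverse events, the first objective needs the same ascertainment in both arms. A rule that reports an event only when an unblinded clinician links it to the intervention gives reports from essentially one arm. It can make MLA look worse, because control events of the same kind go unreported. It can also hide an MLA harm that nobody attributes. The Discussion concedes that prior evidence on skin reactions to MLA is very limited, so attribution has little to rest on.

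**Working it through.** The protocol's one calculated figure is the sample size, and neither point enters it. For completeness, with 50% v 25%, two-sided 5% and 90% power: n = [1.960·√(2·0.375·0.625) + 1.282·√(0.25 + 0.1875)]² / 0.25² = 76.7, so 77 per group, as stated.

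**1. Composite: the passages side by side**

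| Removal because of | Background: route to failure? | In the composite list? | Counted elsewhere? |
|---|---|---|---|
| Occlusion, fracture, thrombosis, dislodgement | Yes | Yes | Individual types |
| Haematoma | Not named | Yes | Not in individual types |
| Infection meeting NHSN/CDC criteria | Yes | No | Infection outcomes, as an infection and not as a removal |
| Suspected infection, never confirmed | Yes (infection) | No | No outcome |
| MARSI | Yes | No | Skin events and SAEs, as an injury and not as a removal |

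The fourth row is the real gap.

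The removal form only partly closes it. Table 1 lists suspected infection and MARSI under complications at removal. The examples under reason for removal are treatment complete, death and routine replacement, followed by an open-ended etc. A complication present at removal is not necessarily its cause.

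*What the omission can hide.* Let b be the rate of failure from the listed causes, equal in both arms, and let i be the rate of additional removals for infection. The composite difference (MLA minus control) is 0 as listed, and (b + i_MLA) − (b + i_control) = i_MLA − i_control once these removals are added. All rates are assumed, with b = 20%:

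| i control | i MLA | As listed | With infective removals | Difference |
|---|---|---|---|---|
| 5% | 5% | 20% v 20% | 25% v 25% | 0 |
| 5% | 2% | 20% v 20% | 25% v 22% | −3 points |
| 10% | 5% | 20% v 20% | 30% v 25% | −5 points |
| 2% | 5% | 20% v 20% | 22% v 25% | +3 points |

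An effect is lost only if infective removals differ by arm.

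**2. Adverse events: what the rule does to equal rates**

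Assume 80 patients per arm, the same true rate r in both arms, a share a of MLA-arm events attributed to MLA, and no control event attributed. Reported events in the MLA arm = 80 × r × a, against 0 in controls. P values are from Fisher's exact test, two-sided:

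| r | True events per arm | a = 25% | a = 50% | a = 75% |
|---|---|---|---|---|
| 5% | 4 | 1 v 0, p = 1.00 | 2 v 0, p = 0.50 | 3 v 0, p = 0.25 |
| 10% | 8 | 2 v 0, p = 0.50 | 4 v 0, p = 0.12 | 6 v 0, p = 0.03 |
| 20% | 16 | 4 v 0, p = 0.12 | 8 v 0, p = 0.007 | 12 v 0, p = 0.0003 |

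Every cell has a true difference of zero. The table applies only to events that reach the data through the reporting rule and by no other route.

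**The case against.** **On the composite.** The definition is identical in both arms, so a reader who infers an unfair comparison goes further than the text allows. The word introducing the list can be read as non-exhaustive, in which case infection is not strictly excluded. Infection is also measured separately, and a blinded infectious diseases consultant apportions those outcomes. Keeping mechanical failure apart from blinded infection endpoints is a defensible choice. All of this stands, and it limits the point to labelling and completeness. It does not remove it. If the list is open, the protocol does not say which other removals count. If it is closed, the all-cause label is wrong. Either way, removals for unconfirmed infection have no assured place.

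A reader might also try to express the missed removals as a share of all failures, using the Background's figure of up to 30%. The documents do not support that: the figure is a literature upper bound for CVADs in general, and no rate of infective removal is given.

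**On adverse events.** A reader might infer that non-serious events in controls are zero by rule. That is wrong for skin and site events: Secondary outcomes and the daily check in Table 1 cover them in both arms without regard to attribution, and a suspected-cause field already exists. The three listed SAEs are likewise recorded whatever the attribution. The statistical methods section also uses the word intervention for both arms, so a control event attributed to the standard dressing might be reportable. Even on that reading, reporting depends on unblinded attribution. What remains is the conflict between unfiltered daily collection and filtered reporting, for events outside those categories.

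**Conclusion.** Both points hold at modest size.

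(a) The composite is mislabelled and incomplete. It omits infection and MARSI, which the Background gives as routes to failure, and removals for suspected but unconfirmed infection count in no outcome. The comparison between arms is not biased. The endpoint can miss a benefit or harm of MLA, but only if such removals differ by arm. On the assumed rates above, the missed difference is 3 to 5 percentage points.

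(b) The reporting rule cannot support the adverse event comparison in the first objective for non-serious events other than those captured by the skin and site checks. On assumed equal true rates of 5% to 20%, reports would run from 1 v 0 to 12 v 0. How many events fall in this remainder cannot be told from the documents, and it may be few.

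The primary outcome and the 77 per group are untouched. The changes are still worth making, because they concern the complications the trial sets out to reduce.

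**What to change.** **Composite.** Add removal for suspected or confirmed infection and removal for MARSI to all-cause CVAD failure. Add infection, MARSI and haematoma to the individual types so that the two lists agree. Make sure the reason-for-removal field has explicit options for suspected infection and MARSI, so that cause is recorded apart from complications present at removal. Keep the blinded NHSN/CDC infection outcomes as they are.

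**Adverse events.** Reconcile the data collection section with the harms section. State that dressing-, skin- and device-related adverse events are recorded and compared in both arms whatever the attribution, with relatedness as a separate field, as the protocol already does for SAEs.

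**Cost.** Outcome wording, a derivation rule, one or two options on the removal form, and slightly more event entry for control patients. Most of the fields already exist. For patients whose removal form is already complete, the reason for removal may need checking against the medical notes.
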